### Specific aims

#### Aim 1 (primary analyses)

Compare the effects of the combined cognitive behavior and physical therapy (CBPT) intervention condition versus a sham control condition on balance confidence and performance-based measures of balance and functional mobility in lower limb prosthesis users.
*Hypothesis 1a*: Participants receiving CBPT intervention will demonstrate improvements in balance confidence over time compared to participants in the control condition.*Hypothesis 1b*: Performance-based measures of balance will improve after CBPT intervention.*Hypothesis 1c*: Performance-based measures of functional ability will improve after CBPT.

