**Fig. 1 Fig1:**
[figure not shown]
Flowchart of study participation

Participants in the intervention condition will complete eight weekly training sessions that include a virtual reality active gaming component (i.e., PT component), with CBT strategies that increase balance confidence by addressing subject-specific avoidance behaviors and maladaptive cognitions. Each session will last approximately 1.5 h. Participants in the control condition will complete a series of at-home upper-body seated exercises during this 8-week period after being taught by a physical therapist how to perform the exercises. The intention of the sham control is to blind participants to the study group. At the start of the study and at 8 (post-intervention), 16, and 24 weeks following group allocation, participants will complete survey-based outcome measures and activity monitoring. At baseline and post-intervention, participants will complete performance-based assessments of balance and of functional mobility. Outcomes measures are described below.

To minimize loss to dropout between baseline and final follow-up, research coordinators will routinely contact participants by telephone and email to maintain engagement in order to maximize participant adherence. Adherence will be quantified based on number of study visits attended and frequency of attendance. If a participant wishes to drop out of the study, they will be queried as to their reasons for doing so and every attempt will be made to address their concerns and to obtain the minimum amount of data necessary to address hypotheses related to the primary outcome (i.e., self-reported measures at 0 and 25 weeks).

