It is expected that 70 participants will be recruited in order to obtain a total of 60 eligible participants (30 intervention and 30 control participants), assuming a 15% drop-out rate. Using G*Power 3.1, a sensitivity analysis (with regard to Hypothesis 1a) was conducted, specifying a power of 0.80, an alpha of 0.05, and an average correlation of observations of 0.50. According to the analysis, with 30 participants in each group we will be able to detect a small to medium effect (f = 0.152) of intervention on ABC score over time with this design, which is consistent with the size of effect observed for older adults [10, 11]. We will have similar power for all hypotheses in Aim 2, which use the same analysis as Hypothesis 1a; we will have power to detect a medium effect size (d = 0.46) for Hypothesis 1b and a correlation of r ≥ 0.42 for Hypothesis 3.

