### Sham-control condition

Participants assigned to the control condition will be introduced to three exercise modules (Modules A–C) that include seated exercises to improve core and arm strength and flexibility. All of the exercises are demonstrated to the participant by a physical therapist at the initial session. Participants will be provided a manual with thorough descriptions and visual aids of the seated exercises. Some of the exercises include use of a resistive (plastic air-filled) ball, which will also be provided to the participant. Participants will be instructed to start with Module A and continue for weeks 1–3, followed by Module B for weeks 4–6, and to finish with Module C for weeks 6–8. Participants will be told to follow the modules at their own pace. Each module includes approximately eight exercises that take 15–20 min to complete and participants will be told to work on the exercises three days per week. Participants will be provided a worksheet to record exercise days. Participants will be contacted by phone every 2–3 weeks during the 8-week intervention period to maintain engagement and encourage completion of the follow-up assessments.

The control is intended to account for a potential placebo effect and is considered a sham-control in that none of the exercises target lower extremity strength or flexibility, which is more likely to induce functional improvements and promote balance confidence during weight-bearing activities.

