### Analysis plan

To test Hypothesis 1a we plan to use a 2 (group) × 4 (time point) mixed ANOVA to examine if there are significant differences in changes in ABC scores between the groups (i.e., an interaction effect), accounting for any missing data. In the event of a significant interaction, a post-hoc paired *t*-test will be used to compare ABC scale in the intervention group at 0 and 25 weeks and independent samples *t*-test to compare ABC scale between groups at 25 weeks.

To test Hypotheses 1b and 1c we will use a paired *t*-test to compare BBS scores and L-test times pre- and post-intervention. H1b and c do not compare time-related changes in performance between groups as they are only intended to assess the immediate effects of intervention.

The same analyses from Hypothesis 1a will be used to test all hypotheses in Aim 2. For Hypothesis 2a, a group × time interaction on self-reported community participation measures (CRIS, FAI, SF36 scales) and objective measures from the activity monitors will be tested. A false-discovery rate correction method will be used to minimize the likelihood of type I errors. For Hypothesis 2b, an interaction on the QoL score will be tested. In the event that H2a is not supported, alternative measures to assess integration will be considered.

To test Hypothesis 3 changes in ABC scores (0 weeks to 25 weeks) will be correlated with changes in self-reported and objective measures of community participation. A false-discovery rate correction method will be administered to minimize the likelihood of type I errors. In the unlikely event that Hypotheses 1a and 2a are not supported, this would not exclude the possibility of an association between subject-specific changes in confidence and participation. In such a case, a significant correlation would suggest that improving balance confidence can increase participation, but for optimum effectiveness of the intervention, one should only train individuals who are most likely to respond to the intervention (show large increase in ABC scores). As an initial step to identify commonality among “responders” we would employ a suite of supervised learning techniques (e.g., cluster and canonical correlation analysis) to explore multidimensional relationships among responses to individual items on the ABC, BBS, CRIS, and SF36.

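### Aim 1 promises a comparison with sham on balance and functional mobility, but Hypotheses 1b and 1c are tested only by pre-post change, so a positive result could not be attributed to CBPT

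*Protocol article*

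**What the plan says.** All references are to the protocol article.

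- **Aim 1**, headed as primary analyses, is to compare CBPT "versus a sham control condition on balance confidence and performance-based measures of balance and functional mobility in lower limb prosthesis users".
- **Hypotheses under Aim 1.** 1a names the control condition as comparator. 1b and 1c do not: "Performance-based measures of balance will improve after CBPT intervention" and "Performance-based measures of functional ability will improve after CBPT".
- **Analysis plan.** "To test Hypotheses 1b and 1c we will use a paired *t*-test to compare BBS scores and L-test times pre- and post-intervention". The next sentence rules out the group comparison: "H1b and c do not compare time-related changes in performance between groups as they are only intended to assess the immediate effects of intervention". Hypothesis 1a and all of Aim 2 are tested by a group × time interaction.
- **Study design.** The performance tests are not confined to one arm: "At baseline and post-intervention, participants will complete performance-based assessments of balance and of functional mobility". Functional abilities adds that blinded assessors administer both tests.
- **Sham-control condition.** "The control is intended to account for a potential placebo effect".
- **Participants.** The planned size is "a total of 60 eligible participants (30 intervention and 30 control participants), assuming a 15% drop-out rate". The detectable effect given for Hypothesis 1b is d = 0.46, at power 0.80 and alpha 0.05.
- **Outcome measures.** The ABC scale is the primary outcome. Functional ability is introduced among the additional secondary outcomes.

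**The concern.** The aim and the test ask different questions. The aim asks whether CBPT does better than sham. A paired test asks whether scores moved between two visits. The reason offered, that only immediate effects are of interest, settles when to measure and leaves open what to compare with. An immediate effect of CBPT is still a contrast with what would have happened by week 8 without it, and the sham arm is there to show that.

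A within-arm change mixes any CBPT effect with several other things:
- practice on the BBS and L-test;
- placebo response, which the control was built to absorb;
- natural recovery: the Background reports that walking ability goes on improving after discharge from rehabilitation, and people may enter after six months on a definitive prosthesis;
- possibly some regression to the mean.

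At stake is the reading of two of the three Aim 1 hypotheses. Either could be reported as supported with no use made of randomisation, although the plan describes data that would allow the randomised comparison.

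**Working it through.** **Inputs.** From Participants: 30 per arm, alpha 0.05 (sidedness not stated), power 0.80, d = 0.46 for Hypothesis 1b. Assumed, because the documents give no value: the shift common to both arms, and the baseline to week-8 correlation ρ of each measure. (The 0.50 in Participants is specified for the Hypothesis 1a calculation.)

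**Step 1. Reproduce d = 0.46.** For a paired t-test, power = P(T > t_crit), where T is noncentral t with n − 1 df and noncentrality d√n. For two independent groups of n, df = 2n − 2 and noncentrality is d√(n/2). Two-sided tests add the lower tail. Solving for 80% power:

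| Test | One-sided | Two-sided |
|---|---|---|
| Paired, n = 30 (one arm) | 0.465 | 0.529 |
| Paired, n = 60 (arms pooled) | 0.325 | 0.368 |
| Two groups, 30 per arm, on change | 0.650 | 0.736 |

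Only the one-arm, one-sided paired test comes close to 0.46 (its power at 0.46 is 0.793). The Analysis plan does not name the arm, but this match and the wording of 1b and 1c point to CBPT alone. The unit is the SD of the change score.

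**Step 2. What the paired test does when CBPT adds nothing.** Let both arms shift by δ SDs of change, so that the true difference between arms is zero. Paired test, n = 30, two-sided, t_crit = 2.045:

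| Assumed δ | Noncentrality δ√30 | P(significant) | Between-arm test |
|---|---|---|---|
| 0.2 | 1.10 | 0.185 | 0.05 |
| 0.3 | 1.64 | 0.355 | 0.05 |
| 0.4 | 2.19 | 0.563 | 0.05 |
| 0.5 | 2.74 | 0.754 | 0.05 |

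With one-sided alpha, which d = 0.46 implies, the figures at 0.2, 0.3 and 0.5 are 0.28, 0.48 and 0.85.

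**Step 3. What a between-arm test can detect** (30 per arm, two-sided, 80% power).

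- t-test on change: 0.736 SD of change.
- ANCOVA on baseline: 0.736 × √(1 − ρ²) in raw outcome SDs. At ρ = 0.5: 0.736 × 0.866 = 0.64. At ρ = 0.8: 0.736 × 0.6 = 0.44.

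These units differ. The SD of change is √(2(1 − ρ)) raw SDs: 1.00 at ρ = 0.5 and 0.63 at ρ = 0.8. The ANCOVA figures are therefore 0.64/1.00 = 0.64 and 0.44/0.63 = 0.70 SD of change. Both are well above 0.46.

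**Step 4. Power at 0.46 SD of change.** The between-arm t-test on change has power 0.42 two-sided. Restoring 80% would need 76 per arm. ANCOVA at ρ = 0.5 has noncentrality (0.46/0.866) × √15 = 2.06 and power of about 0.53.

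**The case against.** The strongest defence is that the test fits the hypotheses it serves. Hypotheses 1b and 1c speak only of improvement after CBPT, name no comparator, and the Analysis plan openly says that no group comparison is made. This is a disclosed choice, not an oversight. That stands, but it moves the mismatch up one level: both hypotheses sit under an aim that is explicitly a comparison with sham, and disclosure does not supply that comparison. Nor is this a detail left to a fuller document, since the article states the choice and gives its reason.

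Other parts of the defence also stand:

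- BBS and L-test are secondary outcomes, even though Aim 1 is headed primary. A reader might infer that the trial's main conclusion loses its randomised basis. It does not: the ABC analysis and all of Aim 2 compare the arms.
- The arm used in the paired test is inferred, not stated. Pooling both arms would not give the comparison either.
- Regression to the mean is probably diluted. Selection is on an ABC score below 80, and the Background calls balance confidence and performance-based balance only moderately correlated.
- A reader might expect a between-arm test to remove the effect of extra laboratory exposure. It would not. CBPT participants attend eight sessions, whereas controls exercise at home after being taught, so that difference remains in any contrast.
- The shifts in step 2 are assumptions. The 19% to 75% should not be read as this trial's false-positive rate.

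**Conclusion.** The point holds as a contradiction between Aim 1 and the Analysis plan for the BBS and L-test, and the stated reason does not resolve it. A significant paired test would show that scores changed, not that CBPT changed them. The paired test keeps its 5% level for its own null of no change. The 19% to 75% (shift of 0.2 to 0.5 SD of change, n = 30, two-sided) is the chance of a significant improvement that owes nothing to CBPT. It rests on the assumed shift, on analysis of the CBPT arm alone, and on complete data for 30.

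The reach is limited to Hypotheses 1b and 1c. The plan describes baseline and post-intervention assessments for participants in general, so as written the remedy needs no new data.

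**What to change.** - Test Hypotheses 1b and 1c between arms at week 8, using both arms. ANCOVA of the week-8 score on randomised group, baseline score and the vascular/non-vascular stratum is preferable. A 2 × 2 group × time interaction would also remove the contradiction and match the trial's other analyses.
- Reword 1b and 1c to name the control condition, and delete the sentence that declines the group comparison.
- Report within-arm changes as descriptive only.
- In Participants, replace d = 0.46 with the two-group figure, stating sidedness and unit: about 0.74 SD of change for 30 per arm, two-sided; or, by ANCOVA, about 0.64 raw SD at an assumed baseline correlation of 0.5 (0.44 raw SD at 0.8).

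**Cost.** The change is to wording and the power statement, with no added assessments. The loss of stated sensitivity is real: between-arm power at 0.46 SD of change is only about 42% with a t-test on change. The article should say plainly that, at this sample size, only larger effects on these secondary outcomes can be detected.

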#### Aim 3 (secondary analyses)

Examine the relationship between changes in balance confidence and changes in community integration following participation in CBPT intervention.
*Hypothesis 3*: For participants in the intervention condition, change in balance confidence from 0 to 25 weeks will be directly correlated with changes in community participation (0 to 25 weeks).

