#### Frenchay Activity Index

The Frenchay Activity Index (FAI) is a 15-item behavioral scale that primarily measures social participation and daily activities (i.e., domestic/chores, work/leisure, and outdoor activities) [25]. Frequency of participation in activities over the last 3–6 months is rated on a four-point scale resulting in a single summary score, ranging from 0 (inactive) to 45 (highly active). The FAI is a valid and reliable measure among users of a LLP (ICC = 0.79) [26]. We will include the measure based on its association with the ABC scale in users with a LLP [4].

Additional secondary outcomes include quality of life and functional ability as described below.

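### If H1a and H2a fail, a within-CBPT correlation of concurrent changes cannot support the planned reading that raising confidence raises participation, or that only likely responders should be trained

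*Protocol article*

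**What the plan says.** Hypothesis 3 (Aim 3, a secondary analysis) is confined to one arm: "For participants in the intervention condition, change in balance confidence from 0 to 25 weeks will be directly correlated with changes in community participation". The Analysis plan repeats the method: "changes in ABC scores (0 weeks to 25 weeks) will be correlated with changes in self-reported and objective measures of community participation". Multiplicity is handled as follows: "A false-discovery rate correction method will be administered to minimize the likelihood of type I errors".

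The Analysis plan then turns to failure of the randomised comparisons: "In the unlikely event that Hypotheses 1a and 2a are not supported, this would not exclude the possibility of an association". Two conclusions follow. The first is about mechanism: "In such a case, a significant correlation would suggest that improving balance confidence can increase participation". The second is about patient selection, for best effectiveness: "one should only train individuals who are most likely to respond to the intervention (show large increase in ABC scores". Exploratory work comes next: "As an initial step to identify commonality among “responders” we would employ a suite of supervised learning techniques".

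The section describes no sham-arm correlation to accompany this reading, and the Limitations section gives no caveat on it.

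**The concern.** H1a and H2a are the tests that use randomisation. If neither is supported, the trial has not shown that CBPT moved confidence or participation relative to sham. What remains is a correlation between two changes measured over the same weeks in the same 30 people. Three things stand between that correlation and the planned conclusions.

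- **Shared causes and direction.** A change in health or mood can move both variables, and more participation can raise confidence as easily as the reverse. The protocol itself relies on an association that exists without this intervention. The Background cites one, and of the Frenchay Activity Index it says: "We will include the measure based on its association with the ABC scale in users with a LLP".
- **No comparison with sham.** Sham participants complete the same surveys and activity monitoring on the same schedule (Study design; Outcome measures). Their data could show whether the association arises without CBPT, but H3 does not use them.
- **Responders defined by outcome.** A large ABC increase is known only after treatment. It names no baseline feature by which to choose whom to train, and it does not show that CBPT caused the gain.

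At stake is that a trial with unsupported primary and secondary comparisons could still report a mechanism and a selection recommendation, both written in advance.

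**Working it through.** **1. The plan's own figure.** The sample-size paragraph under Participants gives a detectable correlation of 0.42 for H3, with power 0.80 and alpha 0.05. Under the point-biserial t model, with noncentrality r/√(1−r²)·√n and n − 2 degrees of freedom, n = 30 gives r = 0.422 one-sided and 0.468 two-sided. The stated 0.42 is therefore reproduced with 30 participants, one-sided, which confirms that H3 was sized on one arm.

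**2. Large ABC gains with no effect.** Input: the plan's average correlation between observations, 0.50.

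- SD of change = SD × √(2 × (1 − 0.50)) = 1 SD.
- With zero mean change and normal scores, P(gain ≥ 1 SD) = 1 − Φ(1) = 0.159, about 5 of 30.
- P(gain ≥ 0.5 SD) = 1 − Φ(0.5) = 0.309, about 9 of 30.

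Entry requires an ABC score below 80, so regression to the mean could raise these shares.

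**3. What the false-discovery-rate step does.** There are nine participation measures: six self-report (two CRIS scales, three SF36 subscales, the FAI) and three from the monitors (steps per day, steps per day outside the home, time outside the home). The documents give no correlation between ABC change and participation change, so the following are assumptions:

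- no treatment effect and no causal path from confidence to participation;
- a change correlation r for each self-report measure that comes from other sources;
- 0 for the monitor measures;
- 0.5 among the nine measures;
- n = 30, two-sided tests, Benjamini-Hochberg at 5%.

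Single-measure figures use the Fisher z approximation; the last column is simulated.

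| Assumed r, self-report | One measure significant | At least one of nine survives |
|---|---|---|
| 0.1 | 8% | about 8% |
| 0.2 | 18% | about 20% |
| 0.3 | 36% | about 41% |
| 0.4 | 60% | about 71% |

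The simulated column moves by one to two percentage points between runs. With r = 0 throughout, the last column is about 5%, as intended. The correction controls findings due to chance. It does nothing about correlations that are real but not causal, and under these assumptions the sham arm would give the same rates.

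**4. What a between-arm comparison can detect.** The standard error of the difference between two Fisher z values with 30 per arm is √(1/27 + 1/27) = 0.272. For 80% power, two-sided, the difference in z must be (1.960 + 0.842) × 0.272 = 0.763. Since tanh(0.763) = 0.64, this corresponds to about r = 0.64 in one arm against 0 in the other.

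**The case against.** The wording is more careful than a quick reading suggests. The correlation must be significant after correction, it would only suggest, and confidence can rather than does raise participation. The preceding sentence, that null group effects do not rule out an association between individual changes, is correct and can stay. The selection sentence speaks of people likely to respond, which is a prediction, and the responder analysis is called an initial step. The authors therefore do not claim that the correlation itself identifies whom to train. All of this stands. Even so, the sentence that one should only train such people carries no hedge of its own, and the exploratory step still starts from a post-baseline label.

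Three stronger readings are tempting, and the documents support none of them.

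- A reader might infer that a failed H1a means CBPT had no effect on anyone, so that every ABC change is spontaneous. A non-significant interaction with 30 per arm does not establish that; effects may be small or differ between people. The point is only that a one-arm correlation cannot tell these cases apart.
- A reader might infer that the rule gives a false conclusion with high probability. That depends on r, which the documents do not supply; at 0.1 or 0.2 the rate is modest.
- A reader might put the association down to how participants felt on the survey day. That fits poorly: the FAI looks back 3–6 months, the quoted CRIS item two weeks, and the monitors record a week and share no self-report error. Longer illness and reverse direction remain.

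**Conclusion.** The point holds in limited form. After unsupported H1a and H2a, a significant H3 correlation in the CBPT arm is an association. It does not support the stated inference about mechanism or the stated recommendation on selection, and this follows from the design without any assumed number. How often the situation would arise does rest on assumptions: about 8% to 71% for non-causal self-report correlations of 0.1 to 0.4, with unrelated monitor measures. The 16% share with a 1 SD gain rests on the plan's correlation of 0.50, normality and zero mean change.

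This should be fixed, but it does not threaten the trial. It is a conditional reading of a secondary aim and alters no primary analysis, sample size or data collection.

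**What to change.** In the Analysis plan paragraph on Hypothesis 3:

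- Delete the inference that a significant correlation suggests confidence can raise participation, and the statement on whom to train. State that if H1a and H2a are not supported, H3 is reported as an association only.
- Compute the same correlations in the sham arm. Report both arms side by side with the between-arm difference and its confidence interval. Say that power for that difference is low (about 0.64 against 0 for 80% power).
- Keep the responder work labelled exploratory. Base any statement on whom to train on baseline features whose relation to outcome is compared between arms.
- Optionally, add ABC change over weeks 0–8 against later participation as a supportive analysis, so that the supposed cause comes first. It remains observational.

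The cost is a few sentences and a small extra analysis on data already being collected, together with a weaker H3 claim. Pooling both arms would lower the detectable correlation (Fisher z, two-sided, about 0.49 at n = 30 and 0.36 at n = 60), but that gain belongs to one pooled correlation and should not be claimed for the between-arm comparison.

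### If Hypotheses 1a and 2a fail, the plan still draws a causal conclusion and an only-train-responders conclusion from a correlation of changes in the CBPT arm alone, which cannot support either

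*Protocol article*

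**What the plan says.** Aim 3 restricts Hypothesis 3 to one arm: "For participants in the intervention condition, change in balance confidence from 0 to 25 weeks will be directly correlated with changes in community participation". The Analysis plan gives the method: "changes in ABC scores (0 weeks to 25 weeks) will be correlated with changes in self-reported and objective measures of community participation". It adds a multiplicity safeguard: "A false-discovery rate correction method will be administered to minimize the likelihood of type I errors".

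The Analysis plan then turns to a trial in which the main comparisons do not succeed: "In the unlikely event that Hypotheses 1a and 2a are not supported, this would not exclude the possibility of an association" between individual changes in confidence and participation. For that outcome it states the reading to be taken: "a significant correlation would suggest that improving balance confidence can increase participation, but for optimum effectiveness of the intervention, one should only train individuals". The people meant are then described as those "who are most likely to respond to the intervention (show large increase in ABC scores").

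The next step is exploratory: "As an initial step to identify commonality among “responders” we would employ a suite of supervised learning techniques". The examples given are cluster and canonical correlation analysis of individual items on the ABC, Berg Balance Scale (BBS), CRIS and SF36.

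The article states no control-arm correlation, no interaction of a baseline characteristic with group and no mediation analysis in support of either conclusion.

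**The concern.** Two inferences are fixed in advance, and neither follows from the analysis described.

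- **The causal reading.** ABC change and participation change in the same people can move together because something else moved both (general health, prosthetic fit, mood, season), because going out more raised confidence, or because both were self-reported on the same occasion. A single-arm correlation does not tell these apart from a path running from confidence to participation.
- **The selection rule.** If Hypothesis 1a is not supported, the ABC gains in the CBPT arm have not been shown to be caused by CBPT. Entry requires an ABC score below 80 (Participants section), so regression to the mean will produce some gainers. Calling large gainers responders assumes the effect that the randomised comparison did not establish. Response is also defined by a post-baseline change, which is unknown when deciding whom to train.

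At stake is the message from a trial whose randomised comparisons were not supportive. The article supplies, in advance, a favourable conclusion drawn from a non-randomised association.

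**Working it through.** **Inputs.** From the Participants section: 30 people per arm, power 0.80, alpha 0.05, and a detectable correlation of r ≥ 0.42 for Hypothesis 3. The power and alpha are stated for Hypothesis 1a and assumed to carry over; sidedness is not stated. From Outcome measures: nine participation measures, made up of three from the monitors, two CRIS scales, three SF36 subscales and the FAI. ABC has 16 items and BBS has 14 tasks. The background correlations used in step 2 are my assumptions; the article gives none.

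**1. The plan's own figure.** Noncentral t model, df = n − 2, δ = √n · r / √(1 − r²), n = 30, power 0.80:
- one-sided alpha 0.05: r = 0.422, matching the stated 0.42;
- two-sided: r = 0.468, or 0.492 by Fisher z.

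With n = 60 the same methods give 0.31 to 0.36. The stated figure therefore fits a test in one arm of 30, as Aim 3 says.

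**2. How often common causes alone would trigger the conclusion.** Suppose CBPT has no effect on either variable, confidence has no effect on participation, and shared influences give a change–change correlation ρ. At n = 30 the two-sided 5% critical value is |r| = 0.361. Simulation gives:

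| assumed ρ | one test significant | at least one of nine significant after false-discovery-rate correction |
|---|---|---|
| 0.2 | 19% | 30% |
| 0.3 | 37% | 60% |
| 0.4 | 61% | 83% |

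The last column takes all nine measures to share the same common factor. At ρ = 0 it is 5%. The correction controls chance findings as intended, but a correlation produced by a common cause is a real correlation and passes through it.

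These are probabilities of detecting a genuine but non-causal association. They are not type I error rates for Hypothesis 3, which claims only that the changes are correlated.

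**3. What the control arm can and cannot settle.** Fisher z for a difference between two correlations with 30 per arm, two-sided 5%, power 0.80:

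(1.960 + 0.842) × √(1/27 + 1/27) = 2.802 × 0.272 = 0.762

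tanh(0.762) ≈ 0.64. The comparison would detect about r = 0.64 against 0, or, since atanh(0.30) + 0.762 = 1.072, about 0.79 against 0.30. It is far too weak to serve as a decision rule.

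**4. The item-level example.** After centring, 30 people leave 29 dimensions. Sixteen ABC items and 14 BBS items span subspaces whose dimensions sum to 30. Since 30 > 29, the subspaces share at least one direction, so the first unregularised canonical correlation is exactly 1 whatever the data. Independent noise gave 1.000 in every one of 300 runs at n = 30 and at n = 26. Pooling 60 people removes the exact saturation, but noise still gives about 0.83 for this pairing and 0.99 for ABC against 36 SF36 items.

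**The case against.** The best defence is that the passage is modest. Aim 3 is secondary, the causal wording is hedged, the case is called unlikely, and the responder search is an initial step. No primary analysis, sample size or randomised contrast depends on it. It is also correct that failure to support Hypotheses 1a and 2a would not exclude an association. All of this stands and limits the weight of the point. It does not rescue the step from association to causation, or the prescriptive statement about whom to train.

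Several stronger readings are tempting, and the documents do not support them:

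- **That CBPT would have been shown to do nothing.** The plan says not supported, which at 30 per arm is compatible with a real or varying effect. The no-effect scenario in the working is an illustration.
- **That a control-arm correlation would refute the mechanism.** If confidence does drive participation, the association should also appear among controls whose confidence changes. A similar correlation in both arms is expected under causation and under confounding alike.
- **That a group-by-change test would settle the matter with more power.** Pooling 60 people sharpens a single common correlation (detectable two-sided r falls from 0.49 to about 0.35 by Fisher z), but that gain does not apply to the difference between arms.
- **That multiplicity is uncontrolled, or that shared reporting error affects every measure.** A false-discovery-rate correction is planned, and three of the nine measures come from step and GPS monitors.
- **That the exploratory step is degenerate as planned.** The article names canonical correlation only as an example and fixes no variable sets, sample or estimator. The saturation result is a warning about one natural implementation. Whether these methods count as supervised learning is terminology.

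**Conclusion.** The point holds as a fault of stated interpretation. The article commits in advance to a causal reading and a selection conclusion that a CBPT-only correlation of changes cannot carry, in exactly the circumstances where the randomised evidence would not back them. The size depends on an unknown background correlation: over the assumed range 0.2 to 0.4, a single n = 30 test would meet the condition for that conclusion 19% to 61% of the time with no causal path at all. The logical objection does not depend on those figures.

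Hypothesis 3 itself, read as a claim of association among CBPT participants, is legitimate. The primary analysis is unaffected. The change is worth making because the wording would otherwise shape how an unsupportive trial is reported.

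**What to change.** 1. Delete the sentence that reads a significant correlation as evidence that improving confidence can increase participation and that only likely responders should be trained. Label Hypothesis 3 associational and hypothesis-generating.
2. Keep the CBPT-arm correlation, and report the same association in the control arm and pooled across arms, adjusted for group and baseline values. Give the group-by-change term with its confidence interval descriptively, not as a decision rule.
3. Base any statement about whom to train on a few baseline scale-level characteristics tested for interaction with randomised group, labelled exploratory.
4. Do not use unregularised item-level canonical correlation at this sample size.

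The cost is small. The control arm already completes the same surveys and activity monitoring, so no new visits or measures are needed. The downside is that Hypothesis 3 is reported in both arms and its conclusion becomes more modest.
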